### Procedures

This project was initiated on April 1, 2021. Data collection began on May 2, 2022, and will continue until May 2, 2023. The publication of preliminary results will be sought following the synthesis of data in spring or summer 2022. A final report will be developed in spring 2023.

Health care workers from the provinces of Nova Scotia and Alberta will be invited to use the chatbot service. Family members of health care workers will also be welcome to participate in the study. Participant recruitment will be conducted via snowball sampling through word of mouth, social media advertisements, physical advertisements, and referrals via our network and partners (including medical professional organizations). Potential participants will be asked to provide informed consent before receiving services from the virtual assistant. Although the participants will be encouraged to register their email address so that the study team can send them voluntary follow-up surveys to evaluate program performance (more on the surveys below), registration will be voluntary. Regardless of registration, the participants will be provided with access to MIRA following the provision of consent.

If a participant registers their email address, they will be provided with 2 voluntary surveys: one at baseline (immediately following use of the chatbot) and a second one at 24 hours following the initial use of the chatbot. The surveys will collect demographic information (eg, year of birth, gender identity, and visible minority status); ask the participants whether they followed through with a recommended resource and the perceived appropriateness of that resource (eg, “Were the resource(s) that MIRA recommended to you during your conversation appropriate?” or “After your conversation with the MIRA, did you follow-up or connect with the resource(s) that the chatbot recommended?”); and assess baseline mental and physical health via the Clinical Outcomes in Routine Evaluation System (CORE-10), a brief, validated 10-item assessment and outcome measurement tool used to assess conditions including anxiety, depression, physical problems, and risk to self [90]. Select items from the Embodied Conversational Agent Trust Questionnaire (ETQ)—for example, “Did you feel that MIRA was competent?” (4-point Likert scale from 0=not at all to 3=completely)—and Acceptability E-scale (AES)—for example, “How much do you agree with the following statements? MIRA gave me information that was relevant to my concern” (5-point Likert scale from “strongly agree” to “strongly disagree”)—are used to assess client satisfaction and acceptability, including perceived usability, benevolence, credibility, and trustworthiness [91].

In addition to the voluntary survey, data will be extracted in aggregate of the general use of the technology to assess effectiveness and engagement, including topics most frequently raised, average time spent on the service, number of resources provided in an average conversation, number of client interactions with links, most frequent recommendations by the chatbot to clients, number of resources recommended by the chatbot in an average conversation, average number of objections raised by clients in conversations, and intent identification and entity extraction accuracy. The use of aggregate data in this manner will be flagged in the consent form preceding the use of the virtual assistant. Participation on the platform will remain anonymous with the exception of the satisfaction surveys (voluntary), which may be temporarily linked via email address to track survey responses at different time intervals (baseline and 24 hours). Following linkages, emails will be permanently deleted and replaced with a randomized participant number to further protect anonymity. Transcripts between clients and the chatbot will be used anonymously to further train and refine the chatbot. The transcripts do not contain any identifiable information and will only be used to improve chatbot functionality. The use of transcripts by the chatbot to serve as a form of memory from which the chatbot will learn and teach itself to perform in a more refined manner is outlined in the consent form provided to the participants. To further protect anonymity, the chatbot has been programmed to remove any personally identifiable information from the transcripts before saving them (eg, if a name is provided, it is omitted from the saved transcript).

There is no standardized approach to evaluate chatbots within the field of health [56,92]. To determine which variables to collect for analysis, our team aggregated findings from several academic studies and reviews that described the technical characteristics, applications, and evaluation measures of chatbots in the field of health [56,92]. In reflection of the findings of these studies, where applicable for the purposes of our study, we chose items from validated tools or items used to evaluate other chatbots (eg, CORE-10, ETQ, AES, and classifier performance measures such as accuracy and precision) to permit cross-comparability where possible between this and existing research and to support efforts to align evaluative measures within the field [56,89,92-94].

### Data Analysis

The effectiveness of the technology will be assessed primarily through data collected via voluntary follow-up surveys and client interactions and engagement with the chatbot. As the use of the chatbot is anonymous, it is not possible to conduct direct follow-up via electronic medical records to confirm the use of any particular service. As such, the research team will primarily rely on information volunteered by clients via the follow-up surveys and chatbot analytics to assess whether clients are successfully connected with recommended resources (by asking them directly).

### Outcome Evaluation

The primary outcome measure will be an analysis of participant responses to follow-up survey questions on a successful connection with resources recommended by the chatbot and the perceived appropriateness of the resources recommended. More specifically, we ask the participants the following questions: (1) “Was/were the resource(s) the MIRA chatbot recommended to you during your conversation appropriate?” (response options: “yes”; “no”; and “other, please specify”) and (2) “After your conversation with the MIRA chatbot, did you follow-up or connect with the resource(s) that MIRA recommended?” (response options: “yes”; “no”; “other, please specify”; and “I prefer not to answer”; if “no,” then the respondent is asked the subsequent question “why not?”).

Assessment of whether the chatbot successfully connected the respondent with appropriate resources will be the number of respondents who answer “yes” to both of these questions. Further consideration will be given to “no” or “other, please specify” responses, where additional detail is shared by the client, to assess rationale for a failed connection (eg, personal choice not to connect or could not successfully reach the resource after attempting to do so). In reflection of previous reports that approximately 24% to 44% of Canadians do not feel that their mental health needs are being adequately met [3,31], we have set a minimum threshold for successful connection with appropriate resources of >50%.

Secondary outcome measures will be an analysis of mental and physical well-being (CORE-10) at the time of use and 24 hours following use, client satisfaction and acceptability (including perceived usability, benevolence, credibility, and trustworthiness), intergroup variation, drop-off and engagement rates, general chatbot use patterns, and exploration of why this intervention may or may not have been supportive or helpful for particular groups.

Chatbot performance will also be evaluated based on additional technical measures identified in reflection of other evaluative works within the field of chatbots in health to allow for the cross-comparability of the findings [56,92,95-97], including an analysis of intent classification accuracy scores, entity recognition accuracy scores, client URL engagement, chatbot rending and response speed, conversational completes, task completion rates measured via binary responses to questions such as “is this what you were looking for?” and “is there anything else I can help you with?,” star ratings by clients at the end of a conversation, client objections, and prompt interruptions.

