#### Interacting With MIRA

Once the client clicks on the MIRA URL [74], they are directed to a webpage with the MIRA chatbot interface. MIRA begins by welcoming the client and asks them for their consent to use anonymized data from the conversation to evaluate and improve its services, with a link to a pop-up with consent information (Multimedia Appendix 2). If the client provides consent, the chatbot then asks a short series of demographic-related questions—employment type, location, and end user (eg, for the client or for someone else; if *someone else*, then the age of the end user is also collected; Multimedia Appendix 3). Following these preliminary questions, the chatbot asks in an open-ended manner (eg, “How can I help you?”) and provides some examples of questions that could be asked in the form of button options (eg, “I want to find programs and services” or “I want to learn coping skills”; Multimedia Appendix 4). If a client asks to “chat” with MIRA or begins expressing feelings opposed to an obvious request for information, eEliza programming will be prompted (Multimedia Appendix 5). The MIRA website, MIRA chatbot, and MIRA Resource Portal (renamed the MIRA Resource Library for the May 2 launch) were tested for compatibility with multiple electronic devices, including tablets, smartphones, and desktop computers, as well as multiple browser applications, including Safari and Chrome.

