The definition of health care worker varies considerably by health authority or administrator. As such, the following numbers were used to determine a general goal post for a target sample size recognizing that the data sources (Alberta Health Services and Nova Scotia Health Authority) may have differing inclusion criteria for what is categorized as a health care worker. There are approximately 240,000 frontline Alberta Health Services workers in Alberta [82], and there are 23,400 health care workers in Nova Scotia [83]. To include family members into sample size calculations, 2011 Statistics Canada estimates on the average number of individuals in a household were used (2.5 per household) [84]. With a 95% CI and 3% margin of error, the sample size target was estimated to be 1066 for Alberta and 1048 for Nova Scotia. More specifically, this sample size refers to the number of participants who consent to using the chatbot. This study will seek to slightly oversample from each province (Alberta: n=1100; Nova Scotia: n=1100). In reflection of the general experiences of other researchers with participation rates for web-based surveys (34%-43% [85-89]), we will aim to collect between 374 and 473 partial and complete baseline surveys and 110 partial and complete follow-up surveys per province. To the authors’ knowledge at the time of writing this paper, this study is the first to evaluate the use of conversational agents or chatbots to support mental health system navigation; as such, the effect size is unknown at the time of the design phase of the study, and power analysis will need to be conducted as the study team actively gathers data to ensure that our sample size is adequate. Therefore, the sample size is subject to re-estimation during the course of this study.

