Participant recruitment will be conducted through snowball sampling via word of mouth, social media advertisements, physical advertisements (study posters and study information posted on physical bulletin boards in hospital staff rooms as well as in newsletters to staff where possible), and referrals via our network and partners (including medical professional organizations). After consenting to take part in the study via a web-based consent form, the participants will be asked if they would like to take part in voluntary follow-up surveys following the use of the chatbot. Regardless of their response, they will then be able to immediately engage with the chatbot. The inclusion criteria are being aged >18 years at the start of the study, being a health care worker or a family member of a health care worker, being located in Alberta or Nova Scotia, being able to speak and read English, and having access to the internet. The chatbot will be developed with the option of adding French and other languages of peoples geographically located within the settlement of Canada in future iterations of the chatbot (eg, Cree, Inuktitut, and Ojibway). The exclusion criteria are individuals aged <18 years, individuals in provinces outside Alberta and Nova Scotia, those with limited comprehension of English, and those without internet access. However, if a client tries to access this service to support an individual aged <18 years or outside the 2 provinces indicated, the chatbot will include cross-Canadian resources that could support them.

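### Both primary survey items presuppose that MIRA recommended a resource and offer no dedicated answer for respondents who were given none, so this failure can be lost from the >50% success rate

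*Protocol article*

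**What the plan says.** Outcome Evaluation in the protocol article gives both primary items with their response options.

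- Item 1 (appropriateness): "Was/were the resource(s) the MIRA chatbot recommended to you during your conversation appropriate", with "response options: “yes”; “no”; and “other, please specify".
- Item 2 (connection): "did you follow-up or connect with the resource(s) that MIRA recommended", with *yes*, *no* and "other, please specify”; and “I prefer not to answer”; if “no,” then the respondent is asked the subsequent question “why not".

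Success is a count of respondents who say yes to both items, held against a threshold of >50%. The denominator of that percentage is not given. Answers of *no* or *other* are to be examined for the reason a connection failed. The two examples of such reasons both start from a recommendation having been made.

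Under Procedures, anyone who registers an email is sent a survey straight after the chat and another at 24 hours, with no condition on what happened in the chat. Under Participants, willingness to be surveyed is asked before the chat: "Regardless of their response, they will then be able to immediately engage with the chatbot". The target counts there include partly completed forms, for example "110 partial and complete follow-up surveys per province".

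The MIRA Portal section says only that a recommendation can be made during or at the end of a dialogue. Interacting With MIRA describes a free-conversation mode: if the client asks to chat or "begins expressing feelings opposed to an obvious request for information, eEliza programming will be prompted". The secondary outcomes include "drop-off and engagement rates".

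**The concern.** Finding nothing for a person who wanted a resource is the plainest way a navigation chatbot can fail. The primary items are not worded for that person, because both refer to a resource that in their case does not exist. Three things can follow. The respondent may explain under *other*. The respondent may answer *no*, which on item 1 reads as an unsuitable recommendation and carries no reason probe. Or the respondent may see that the items do not apply and skip them.

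The third route matters most. If skippers are left out of the denominator, the rate becomes one among people who were given something. The stated hypothesis is about connecting users with appropriate resources, and the >50% threshold is the article's only pass mark for it.

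Handling of blank items could reasonably sit in an analysis plan. The wording of the items could not be repaired there. If the survey does not record that nothing was recommended, an analyst cannot tell these respondents from others who left the items blank.

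**Working it through.** **Is the event possible, and can it be recovered later?**

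1. Recipients: all email registrants (Procedures), with willingness to be surveyed asked before the chat (Participants). The chat's result does not screen who is surveyed.
2. Occurrence: a recommendation is possible but not assured (The MIRA Portal), and free conversation is allowed (Interacting With MIRA).
3. Recovery: Procedures describes resource counts extracted in aggregate, as an average per conversation. Email linkage is described only between the two surveys, and transcripts are reserved for improving the chatbot. No link from a survey to its chat is described.

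**What size could the effect have?** The article gives no share of respondents without a recommendation and no expected success rate, so there is no plan figure to reproduce here. The values below are assumptions. Let *s* be the success rate over all respondents and *k* the share who were given nothing, skip both items and are left out. Then

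observed rate = *s* / (1 − *k*).

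If only half of those given nothing skip, and the rest answer *no* or *other* and stay in as non-successes, then

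observed rate = *s* / (1 − *k*/2), with *k* now the share given nothing.

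| *s* | *k* | all skip | half skip |
|---|---|---|---|
| 45% | 10% | 0.45/0.90 = 50.0% | 0.45/0.95 = 47.4% |
| 45% | 15% | 0.45/0.85 = 52.9% | 0.45/0.925 = 48.6% |
| 45% | 20% | 0.45/0.80 = 56.3% | 0.45/0.90 = 50.0% |
| 48% | 5% | 0.48/0.95 = 50.5% | 0.48/0.975 = 49.2% |

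A rate of exactly 50.0% does not exceed the threshold. With full skipping, three of the four cases pass. With half skipping, none does.

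**The same in counts.** Take the 110 follow-up surveys planned per province. If all count, a pass needs 56 double-yes answers (56/110 = 50.9%).

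| given nothing and left out | remaining | double-yes needed | as share of all 110 |
|---|---|---|---|
| 11 (10%) | 99 | 50 | 45.5% |
| 22 (20%) | 88 | 45 | 40.9% |
| 33 (30%) | 77 | 39 | 35.5% |

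**How large a share changes the result?** Let *p* be the double-yes rate among those given a resource and *f* the share given nothing. The rate over all respondents is (1 − *f*)*p*, which falls to 50% at *f* = 1 − 0.5/*p*. That is 3.8% for *p* = 52%, 9.1% for 55%, 16.7% for 60% and 28.6% for 70%. The choice of denominator matters when the result is near the threshold and matters little when it is well above.

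**The case against.** The strongest case on the other side is that nothing in the article removes these people. A reader might infer that they have no way to report what happened, or that the failure drops out by design. The text does not support either inference. Both items offer a free-text *other*, and a *no* on item 2 opens a reason question. Neither answer is a double yes, and the article says such answers will be examined. Over all respondents they are non-successes and there is no inflation. Inflation needs two further steps that are not stated: the respondents skip, and skippers are excluded. This stands, and it limits the point to a possible loss.

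A reader might also infer that a failed retrieval can never be told apart from a poor recommendation. That is too strong, since the reason question on item 2 can reveal it. What remains is that a bare *no* on item 1 has no probe of its own.

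The full questionnaire is not shown, so a filter or skip rule may exist in it. That stands as a caveat. The response options of the two primary items are given, however, and none covers this case.

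Some supporting text is weaker than it looks. Developing MIRA presents free conversation as coming before a request for resources, and drop-off is not defined as ending without a recommendation. The event is possible, but nothing shows that it is common among people who answer surveys.

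Task completion, client objections and conversation-level analytics also bear on retrieval failure. They help describe the tool, but they are not described as linked to survey respondents and do not enter the >50% criterion.

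Finally, the outcome is worded as connection with recommended resources, so a rate among those given one fits that wording. Counting every chat without a recommendation as a failure would also penalise users who only wanted to talk. This stands and shapes the fix.

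**Conclusion.** The point holds in a limited form. Both primary items assume a recommendation, go to registrants regardless of whether one was made, and lack a dedicated answer for none. With no stated denominator, partly completed forms accepted and no described link to the chat record, respondents who were given nothing can disappear from the success rate or be mixed with those given something unsuitable.

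The size is unknown. On the assumed figures, full skipping by 15% or 20% lifts a true 45% to 52.9% or 56.3%, and full skipping by 5% lifts 48% to 50.5%. These are worst cases: they assume a true rate just under the threshold, that everyone affected skips, and that skippers are excluded. If half of those affected skip, none of the cases examined passes. This is an inexpensive improvement to the measure that carries the primary conclusion. It does not show that the planned rate is biased.

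**What to change.** 1. Add an answer stating that MIRA did not recommend a resource, or a one-line filter before item 1. Follow it with a question on whether the person was looking for a resource.
2. State the denominator of the >50% criterion: all respondents who sought a resource, with none recommended counted as a non-success. People who were given nothing and were not looking for anything are reported separately.
3. Report the double-yes rate among those given a resource as a secondary figure.
4. Extend the existing reason question to a *no* on item 1.

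The cost is one or two extra survey items, an ethics-board notification and possibly a slightly lower success figure. The article says data collection has begun, so responses gathered before the change would lack the new item and should be identified in the report.

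### The primary connection item accepts either following up or connecting, so some failed attempts to reach a service can be scored as successful connections

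*Protocol article*

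**What the plan says.** Outcome Evaluation in the protocol article bases the primary outcome on "follow-up survey questions on a successful connection with resources recommended by the chatbot and the perceived appropriateness of the resources recommended". Two items carry it. One asks whether the recommended resources were appropriate. The other asks "did you follow-up or connect with the resource(s) that MIRA recommended", with the answers *yes*, *no*, a free-text *other*, and a refusal option. A *no* leads to a question about the reason; a *yes* leads to nothing further.

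Success is "the number of respondents who answer “yes” to both of these questions", and the threshold for it is more than 50%.

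The section then turns to failures: "Further consideration will be given to “no” or “other, please specify” responses". One of its two examples of a failed connection is a respondent who "could not successfully reach the resource after attempting to do so".

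Data Analysis explains why no outside check is available: "it is not possible to conduct direct follow-up via electronic medical records to confirm the use of any particular service". The team relies mainly on survey answers and chatbot analytics.

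**The concern.** The item joins two acts with 'or'. Following up can mean only trying; connecting means reaching. Someone who phoned a service and got no answer did follow up, so *yes* is a truthful reply. If that person also thought the resource appropriate, the scoring rule counts a success. Yet the section itself classes an unsuccessful attempt as a failed connection. The people it names as failures are looked for only where they answered *no* or *other*, and no listed item separates a *yes* that means tried from a *yes* that means reached.

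This is a different matter from the acknowledged reliance on self-report, because here an honest and accurate answer is still put in the wrong class. At stake is what the primary result means. A proportion above 50% could not be read without qualification as successful connection, which is what the study hypothesis claims.

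**Working it through.** **The plan's own figures.** This point disputes none of them. The sample size targets reproduce from n0 = 1.96² × 0.25 / 0.03² = 1067.07, taking p = 0.5 (the document states no proportion), with n = n0 / (1 + (n0 − 1)/N).
- Alberta: N = 240,000 × 2.5 = 600,000 gives 1065.2, rounded up to 1066.
- Nova Scotia: N = 23,400 × 2.5 = 58,500 gives 1047.97, rounded up to 1048.

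Neither target depends on how the item is worded.

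**The statements set side by side (Outcome Evaluation).** Take a respondent who tried a recommended service, did not reach it, and thought it suitable.
1. Construct: connection was not successful, so this is a failure.
2. The section's own example: an attempt that did not reach the resource is a failed connection, so again a failure.
3. Item as worded: the respondent followed up, so *yes* is accurate.
4. Scoring rule: *yes* to both items, so a success.
5. Search for failures: confined to *no* and *other*, so this respondent is not examined.

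Steps 1 and 2 disagree with step 4, and step 5 cannot repair it.

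**Could other data correct it?** The appropriateness item does not, since suitability can be judged without reaching the resource. Link interactions are extracted in aggregate (Procedures) and URL engagement is an additional technical measure (end of Outcome Evaluation). Neither enters the success rule or reclassifies an individual. A click also cannot show that a telephone or in-person service was reached.

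**Where it applies.** Resource Types lists health system navigation resources (with phone numbers, addresses and hours), informational references, and simple textual answers. Trying and reaching come apart mainly for the first. For the other two, opening or reading the resource is connecting with it.

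**Illustration of size.** The documents give no share of respondents who tried, failed and still answered *yes* to both. Let t be the true success rate and m that share, both assumed. The recorded rate is t + m. The chance of recording more than 50% is an exact binomial tail: at least 56 of 110 for one province (Participants plans 110 partial and complete follow-up surveys each), or at least 111 of 220 pooled. All surveys are taken as analysable.

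| n | t | m = 0 | m = 0.05 | m = 0.10 | m = 0.15 |
|---|---|---|---|---|---|
| 110 | 0.40 | 0.013 | 0.125 | 0.462 | 0.831 |
| 110 | 0.45 | 0.125 | 0.462 | 0.831 | 0.979 |
| 220 | 0.40 | 0.001 | 0.060 | 0.473 | 0.922 |
| 220 | 0.45 | 0.060 | 0.473 | 0.922 | 0.998 |

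The table shows how sensitive the threshold comparison would be near 50%. It does not estimate what will happen.

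**The case against.** The best defence is that the wording is only loose. Procedures describes the same item as asking whether participants followed through with a resource, so the two verbs may be meant as near-synonyms. The authors foresaw failed attempts and gave them somewhere to go: *no* with its reason, or the free-text *other*. Many failed attempters will use these, and some who could not reach a resource may also decline to call it appropriate. All of this stands as a limit on size. It does not remove the conflict, because nothing in the item directs a failed attempter away from *yes*.

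The defence is also right that MIRA is informational and that much of its library consists of pages, media and short answers. For those there is little gap between attempt and success, so the point is confined mainly to services and programmes.

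A reader might infer that the primary rate is therefore biased upward overall. The documents do not support that. The item asks about action after the conversation, while The MIRA Portal section says a resource can be delivered at any time during it, so someone satisfied within the chat may answer *no*. Someone who connects more than 24 hours after use is also missed by the second survey. These errors lower the count, and nothing in the documents weighs them against the upward one.

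A reader might also infer that at 24 hours many contacts will still be mere attempts. The document gives no information on how long contacts take, and a slow contact may equally be reported as *no*.

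Finally, the 45% (or 40%) true rate and the 5, 10 and 15 point shares are assumptions. A rate placed just under a threshold crosses it by construction once points are added.

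**Conclusion.** The point holds in a limited form. The protocol fixes an item and a scoring rule under which its own example of a failed connection can truthfully be counted as a success, and it has no step that would detect this. The effect falls mainly on health system navigation resources. This mechanism can only add to the success count; its share is unknown, and the item's net bias is not established. The illustrated probabilities rest wholly on assumed values and show only that a misclassified share of a few percentage points would matter if the true rate lay near 50%. The outcome remains usable, but its label claims more than the item measures. The change is worth making and does not call the design into question.

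**What to change.** Keep the existing item and add one probe after *yes*, for example: 'Did you reach the resource or obtain the information or service?' Count success as appropriate = *yes* and reached = *yes*. Also report the existing *yes*-to-both count for all respondents, so that surveys from before and after the change can still be pooled on that definition. For surveys collected before the change, label the result self-reported follow-up or connection and do not call it successful connection.

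Replacing the item outright would be worse. Data collection began on May 2, 2022, and new wording would split a primary outcome that expects only 110 follow-up surveys per province into two definitions that cannot be pooled.

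The cost is one extra item, an amendment at each of the two ethics boards, and fewer surveys under the stricter definition. For scale, at p = 0.5 the 95% margin with 110 surveys is 1.96 × √(0.25/110) = 9.3 percentage points. If half were collected before the change (an assumption), 55 would remain, and the margin would be 1.96 × √(0.25/55) = 13.2 points.

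### The >50% success rule counts only survey respondents; at the planned follow-up numbers, response related to outcome could move the result across 50% in either direction

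*Protocol article*

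**What the plan says.** All references are to the protocol article.

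- **Outcome Evaluation** takes the primary outcome from follow-up survey questions. The success count is: "Assessment of whether the chatbot successfully connected the respondent with appropriate resources will be the number of respondents who answer" yes to both questions (was the resource appropriate, and did the respondent connect with it). The threshold is >50%. No denominator is written beside it, and nothing says how people who do not answer are counted.
- **Participants** gives the per-province target as "between 374 and 473 partial and complete baseline surveys and 110 partial and complete follow-up surveys per province". The main sample size target has a different unit: "this sample size refers to the number of participants who consent to using the chatbot".
- **Procedures** describes two voluntary surveys for people who register an email address: "one at baseline (immediately following use of the chatbot) and a second one at 24 hours following the initial use of the chatbot". It says the surveys cover demographics, appropriateness, follow-through and CORE-10. The two can be linked by email, after which a random participant number replaces the address.
- **Limitations** acknowledges a risk of response bias. It lists oversampling, clear anonymity, validated tools, neutral response options and, where possible, weighting to census data.

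**The concern.** A proportion among respondents describes the surveyed users only if answering is unrelated to the outcome. Here the outcome is whether the person connected with a suitable resource, and the survey asks about exactly that, so a relation is plausible. Someone who found something useful may be readier to reply, and so may someone who was let down. With about a quarter of baseline respondents targeted for follow-up, even moderate selectivity matters.

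The Discussion makes a wider offer of the chatbot to the Canadian public conditional on its being shown effective. A pass or a failure produced by who replied would bear directly on that.

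**Working it through.** **1. The plan's own figures.**

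Inputs from Participants: "With a 95% CI and 3% margin of error, the sample size target was estimated to be 1066 for Alberta" (1048 for Nova Scotia); 240,000 and 23,400 workers; household size 2.5; 1100 consenting participants planned per province; survey participation 34-43%. A proportion of 0.5 is assumed, since none is stated.

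- n0 = 1.96² × 0.25 / 0.03² = 1067.07. Finite population correction: n0 / (1 + (n0 − 1)/N).
- Alberta, N = 240,000 × 2.5 = 600,000: 1065.2, rounded up to 1066. This matches.
- Nova Scotia, N = 23,400 × 2.5 = 58,500: 1047.97, rounded up to 1048. This matches.
- Baseline surveys: 0.34 × 1100 = 374 and 0.43 × 1100 = 473. Both match.
- Follow-up surveys: 110 is 10% of 1100. No source is given for this rate.

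**2. Share of baseline respondents observed at follow-up** (assuming returners are a subset of baseline respondents).

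- 110/374 = 29.4%, so 70.6% unobserved.
- 110/473 = 23.3%, so 76.7% unobserved.
- Pooling the provinces doubles every count and leaves these fractions unchanged.

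**3. Reversal point.** With s successes among the 110, the rate in all B baseline respondents equals 50% when success among those lost is (0.5B − s)/(B − 110). The document gives no expected success rate, so s is assumed over a range.

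| Successes among 110 | B = 374 | B = 473 |
|---|---|---|
| 56 (50.9%, smallest pass) | 131/264 = 49.6% | 180.5/363 = 49.7% |
| 66 (60%) | 121/264 = 45.8% | 170.5/363 = 47.0% |
| 77 (70%) | 110/264 = 41.7% | 159.5/363 = 43.9% |
| 44 (40%, a fail) | 143/264 = 54.2% | 192.5/363 = 53.0% |

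In the first three rows a pass reverses if the lost fall below the figure shown. In the last row a failure reverses if the lost exceed it. At 60% observed, the gap needed is 13 to 14 points (60 − 47.0; 60 − 45.8).

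With no assumption about those lost, 66 successes among 110 are compatible with:

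- B = 374: 66/374 = 17.6% up to (66 + 264)/374 = 88.2%.
- B = 473: 66/473 = 14.0% up to (66 + 363)/473 = 90.7%.

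**4. How selective response would have to be.** Let p be the true success rate and k the response rate of successes divided by that of failures. The expected observed rate is pk/(pk + 1 − p).

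- True 40%: reaching 56/110 needs k of about 1.56. For B = 374 this is 56/149.6 = 37.4% of successes replying against 54/224.4 = 24.1% of failures.
- True 40%: the binomial chance of at least 56 of 110 is 1.3% at k = 1, 46% at k = 1.5 (expected rate 0.6/1.2 = 50%) and 92% at k = 2 (0.8/1.4 = 57.1%). The k values are assumptions.
- The mirror case is a true 60% with failures replying 1.5 times as often: 0.6/(0.6 + 0.4 × 1.5) = 50%, which does not exceed the threshold.

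**The case against.** Several objections have force.

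- **No attrition rate is stated.** A reader might infer that the plan expects to lose 71-77% of baseline respondents. The article does not say so. The 110 and the 374 to 473 are collection targets that include partial surveys, and the loss follows only if returners are a subset of baseline respondents.
- **The time point is not fixed.** Elsewhere the article uses follow-up surveys for both post-use surveys, and Procedures places both key questions in both. The 24-hour survey is the likelier source, because Participants separates baseline from follow-up and a survey given straight after use leaves little time to connect. It remains a reading. If baseline answers were used, 57-66% of the 1100 consenting users (627 to 726) would still be unobserved.
- **The direction is unknown.** A reader might infer that the bias favours the chatbot. Nothing in the document establishes this. Disappointed users may also be motivated to reply, and those answering no are asked why.
- **The plan does address response bias.** It names the risk and lists measures, and it also draws on chatbot analytics such as link use, task completion and star ratings, which do not depend on the survey. This is fair. But oversampling adds respondents without changing who replies, census weighting corrects demographic imbalance only, and the article does not say how analytics would alter the >50% rule.
- **Missing-data methods belong in an analysis plan that is not shown.** True, and their absence is not the point made here. The respondent-only count and the threshold are fixed in this article.
- **The 60% is illustrative, and wide bounds follow from any survey with low response.** They show vulnerability, not actual bias.

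**Conclusion.** The concern holds in a conditional form. At the targeted numbers, and if the primary answers come from the 24-hour survey with returners a subset of baseline respondents, 71-77% of baseline respondents are unobserved. A result among the remaining 23-29% can then cross 50% in either direction through response related to outcome. Under the assumed 60% success in returners, a gap of 13 to 14 points between returners and those lost is enough to reverse a pass.

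The documents do not support saying that the chatbot would be favoured, that this loss is forecast, or that response bias was overlooked. They do support saying that the survey and denominator behind >50% need stating, and that the listed safeguards do not reach response that depends on having connected.

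**What to change.** 1. State which survey supplies the two primary answers and which denominator the >50% threshold uses.
2. Keep the observed proportion, described as applying to respondents.
3. Report three things beside it from the linked baseline data:
   - returners compared with non-returners on the baseline appropriateness answer, CORE-10 and demographics;
   - the success proportion weighted or imputed to all baseline respondents;
   - the success rate among non-returners at which the >50% conclusion would reverse.
4. Do not claim success for users generally if the conclusion fails under these analyses.

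No special timing is needed, because linked records survive under a participant number once emails are deleted.

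**Cost.** Wording and analysis only, with no new data. The adjusted estimate will be less precise and may be lower. It corrects only for measured baseline differences, so it cannot be relied on to remove selection that arises from connecting after the baseline survey. It also does not cover the 57-66% of consenting users without a baseline survey.
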